## **1.2 Importance and Rationale of Study**

COVID-2019 is a novel strain of enveloped RNA virus that emerged as a deadly virus from Wuhan, China and led to an international pandemic. Common symptoms at the onset of disease mimic influenza and include fevers, non-productive cough, myalgia, and fatigue. The largest experience to date comes from China where the majority of patients (81%) with a confirmed diagnosis of coronavirus 2019 experienced only mild symptoms and did not require hospitalization or further therapy beyond support treatment. However given the latency of the disease and prolonged incubation period even patients who present with mild symptoms may progress to requiring hospitalization, prescription medication therapy, mechanical ventilation, and/or even death.

Currently, there are no FDA approved therapies for the symptom management of COVID-2019. Limited data suggests that hydroxychloroquine, remdesivir, tocilizumab, and convalescent antibody may have a role on the impact of symptoms in patients affected with the disease. However, besides hydroxychloroquine the other therapies are limited to patients with severe manifestations of the disease including development of acute respiratory distress syndrome and require approval from institutional review boards, institutions, companies, and/or the federal government to receive therapy. IV Ascorbic acid is being studied for the effects on symptoms in patients with COVID-2019 in China and the United States. Given the limited therapy available for patients, we wanted to study the impact of high dose of ascorbic acid and zinc gluconate on symptoms of COVID-2019 in patients who present in and receive a confirmed diagnosis.

#### **Biological Effects/Feasibility**

Zinc is known to be important for immune function and has a role in antibody and white blood cell production. Zinc supplementation has been shown to increase polymorphonuclear cells' ability to fight infection, while there is evidence that zinc deficiency increases pro-inflammatory cytokines and decreases the production of antibodies. Zinc has also been implicated in coronavirus biology. Angiotensin-Converting-Enzyme 2 is a zinc metalloprotease that is important for cellular entry of coronavirus. In addition, studies on SARS, a coronavirus, have shown that zinc can inhibit its RNA polymerase.

Vitamin C is known to be an antioxidant and a variety of studies have suggested that vitamin C can impact the immune system. Moreover, in vitro and in vivo studies in avians have shown that vitamin C could be protective against coronavirus and human trials have found that

vitamin C may decrease susceptibility to viral respiratory infections and pneumonia. As a result of these biologic effects, we hypothesize zinc and vitamin C supplementation may have a potential role in improving the response to an infection such as COVID-2019.

The purpose of the current study is to see whether ascorbic acid and zinc gluconate which has limited side effect profile and is readily available over the counter can decrease the duration of symptoms seen in patients with new diagnosis of COVID-2019. A secondary purpose is to see whether Zinc and/or Ascorbic acid supplementation can prevent progression of the severe manifestations of the disease including development of dyspnea and acute respiratory distress syndrome which may require hospitalization, mechanical ventilation, and or lead to death.

### **1.3 Brief summary of relevant literature:**

A Medline literature search with the following unique search terms; coronavirus 2019 was performed.

The relevant literature was summarized in the rationale section above. Briefly, there is variable data about ascorbic acid and vitamin C, but there is evidence that high doses of ascorbic acid (vitamin C) and zinc gluconate reduce duration of common cold symptoms and decrease the severity of symptoms. Furthermore, it is known that majority of patients infected with coronavirus 2019 have mild symptoms that do not require any therapy besides supportive care. In addition, a review of a meta-analysis investigating the role of IV vitamin C in critically ill patients showed no significant effect on mortality but showed variable effects on secondary endpoints including duration of ventilator support and hospital length of stay. What is unknown is whether ascorbic acid and zinc gluconate can shorten the duration of the disease and whether it can prevent progression of the disease.

## **2.0 Study Design, Objective, and Clinical Endpoints**

This is a prospective, randomized study which plans to enroll 520 patients with a principal diagnosis of COVID-2019, managed in an outpatient setting, who presented after being sent by a healthcare provider to get tested and receive a PCR-assay based confirmed diagnosis of the disease. All patients who agree to participate in the study will answer a baseline questionnaire about their symptoms at the time of inclusion. Patients will then be randomized to one of 4 study arms. Patients in Arm A (n=130) will receive 8000 mg of vitamin C (to be taken divided over 2-3 times a day with meals) for 10 days after positive diagnosis. Patients in Arm B (n=130) will receive zinc gluconate 50 mg for 10 days, to be taken at bedtime, after positive diagnosis. Patients in Arm C (n=130) will receive 8000 mg of vitamin C (to be taken divided over 2-3 times a day with meals) and zinc gluconate 50 mg for 10 days (taken at bedtime). Patients in Arm D (n=130) will not receive any of the study medications and continue on standard of care.

Patients will then track their symptoms daily from day 0 to day 28 answering 12 basic questions on illness severity. Symptom assessment tools will be completed by patients daily either electronically or on paper. For those completing the tool electronically a tool will be emailed to the patient daily via RedCap. For those completing the tool on paper a 28 day paper assessment tool will be provided to the patient at the time of consent via email/courier/text/express mail. For those patients completing a paper tool, a research staff member will contact the patient daily via phone call to obtain their daily assessment scores. Study team members will call patients at days 7, 14, 21, and day 28 of the study period to obtain information regarding hospitalizations, ER visits, additional medications prescribed by a healthcare provider

or over the counter, and any side effects from the study supplements that the patient could have experienced. Study team members may also call patients if non-compliance with completion of the daily symptom assessment tool.

Patients seen in the Emergency Department (ER) during the course of study participation will continue to take study supplement(s) (if within the initial 10 days) and continue daily symptom assessments as above.

Patients admitted to the hospital during the course of study participation will no longer be required to continue study supplementation nor track their daily symptoms.

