| Title              | Coronavirus Disease 2019- Using Ascorbic acid and Zinc Supplementation ( CovidAtoZ ) Research Study                                                                                                                                                                                                                                                                                                                                                                                                                                                                                                                                                                                                                                                                                                                                                                                                                                                                            |
| Purpose            | The primary objective of this study is to determine if ascorbic acid (vitamin C) and zinc gluconate result in shortening the duration and type of symptoms and prevention of hospitalizations in patients with confirmed new diagnosis of coronavirus disease 2019 (COVID-19)                                                                                                                                                                                                                                                                                                                                                                                                                                                                                                                                                                                                                                                                                                         |

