(none of these additional supplements). These supplements will be given to patients for a duration of ten days as a part of the study. Patients will be asked to track their symptoms of systemic illness on a daily basis.(Appendix A: Symptom Assessment Tool). We will track 12 symptoms on a scale of 0-3 as follows: A) Temperature Scale (if patient has a thermometer): 0 =  $\leq 98.6$ , 1 =  $> 98.6 - 100.6$ , 2 =  $> 100.6 - 102.6$ , 3 =  $> 102.6$ ; If no thermometer: 0= No fever & no chills, 1= No fever & chills, 2= Fever & no chills, 3= Fever & chills B) Cough Scale: 0 = no cough, 1 = mild, 2 = moderate, 3 = severe C) Shortness of breath: 0 = no shortness of breath, 1 = with moderate intensity exercise 2 = with walking on flat surface 3 = short of breath with getting dressed or daily activities D) Fatigue: 0 = No fatigue/energetic, 1=mild fatigue, 2=moderate fatigue, 3=severe fatigue E) Muscle or body aches: 0 = No muscle or body aches, 1=mild muscle or body aches, 2=moderate muscle or body aches, 3=severe muscle or body aches. F) Headache: 0 = No headache, 1=mild headache, 2=moderate headache, 3=severe headache G) New loss of taste: 0 = No loss of taste, 1=mild loss of taste, 2=moderate loss of taste, 3=severe loss of taste H) New loss of smell: 0 = No loss of smell, 1=mild loss of smell, 2=moderate loss of smell, 3=severe loss of smell I) Congestion or runny nose: 0 = No congestion or runny nose, 1=mild congestion or runny nose, 2=moderate congestion or runny nose, 3=severe congestion or runny nose J) Nausea: 0 = No nausea, 1=mild nausea, 2=moderate nausea, 3=severe nausea K) Vomiting: 0 = No vomiting, 1=mild vomiting, 2=moderate vomiting, 3=severe vomiting L) Diarrhea: 0 = No diarrhea, 1=mild diarrhea, 2=moderate diarrhea, 3=severe diarrhea. Each patient will have a composite score ranging from 0-12/day. The tracking will continue for the 28 days of study participation for each subject. They will also be asked to complete a questionnaire at the beginning of study period, day 7, day 14, day 21 and day 28. The purpose of the

questionnaire is to assess whether patient received additional medications/ supplements, sought treatment at emergency rooms or were hospitalized, or experienced side effects from the study supplements.

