## **2.1 Primary Objective**

The primary objective will be evaluating the duration of symptoms in the four study arms. We will assess this by counting from when peak symptom score is achieved to when there is a 50% reduction in the symptom severity score.

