### 246 **5.3 Secondary Endpoints**

247 Additional endpoints to be considered include:

248 A) Number of days required to reach a total score of 0

B) Individual severity of illness scores (fever, cough, shortness of breath, fatigue)

C) Cumulative severity score at day 5 of the study

D) Emergency room visits

E) Hospitalizations

F) Adjunctive prescribed medications

G) Side effects of supplementation

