## **5.4 Analytical Plan**

Descriptive statistics will be generated for all baseline patient characteristics, complications, and endpoints. Frequency counts and percentages will be used to summarize binary and categorical data. Continuous data will be summarized using means  $\pm$  standard deviation, median and interquartile range, and minimum/maximum values. ANOVA tests will be used to describe the difference in number of days to a 50% reduction on the symptom severity score between the four groups. All pairwise comparisons will be generated and adjusted for multiple comparisons using the Tukey method.

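### A patient admitted to hospital before the symptom score has halved has no value for the primary ANOVA, which biases the comparison if admission differs by arm and admitted patients recover more slowly

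*Protocol*

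**What the plan says.** - Section 1.1 sets the general diary rule: "The tracking will continue for the 28 days of study participation for each subject". Section 2.0 repeats it: "Patients will then track their symptoms daily from day 0 to day 28 answering 12 basic questions on illness severity".
- Section 2.0 then treats two groups differently. Patients seen in the emergency department "continue daily symptom assessments as above". Patients admitted to hospital "will no longer be required to continue study supplementation nor track their daily symptoms".
- Section 2.1 measures the primary outcome by "counting from when peak symptom score is achieved to when there is a 50% reduction in the symptom severity score". Section 5.2 defines the same endpoint.
- Section 5.4 fixes the test: "ANOVA tests will be used to describe the difference in number of days to a 50% reduction on the symptom severity score", with Tukey-adjusted pairwise comparisons. It gives no value, censoring rule or composite outcome for a patient who leaves the diary before the score has halved.
- Admission is itself an outcome of interest. The synopsis purpose includes "prevention of hospitalizations in patients with confirmed new diagnosis of coronavirus disease 2019", and section 5.3 lists "E) Hospitalizations" among the secondary endpoints.
- The section 4.1 schedule records hospitalisations at days 7, 14, 21 and 28, and vital status at day 28.

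**The concern.** The endpoint can be calculated only from daily scores that continue until the score has halved. The protocol lifts the duty to record them at admission, and ANOVA needs a completed number of days for each patient it includes. It has no place for a patient who has not reached the endpoint. A patient admitted or dead before halving is therefore left without a primary outcome.

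This loss is unlikely to be random. Admission usually marks worsening illness, and it occurs after randomisation. The trial also hypothesises that the supplements reduce it. If they do, standard of care loses more slow recoverers, its observed mean falls, and the supplements' benefit looks smaller than it is. If a supplement raised admissions, its arm would look faster. Either error falls on the trial's main question.

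**Working it through.** **Planned power.** Section 5.1 gives 130 per arm, SD 3, V = 0.188 and two-sided alpha 0.05. Means of (6, 5, 5, 5) give V = 0.1875. The noncentrality is N × V / SD² = 520 × 0.188 / 9 = 10.86, with 3 and 516 degrees of freedom. Power is 79.5%, which agrees with the stated 80%. All 520 = 4 × 130 patients are needed for that figure.

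**Bias formula.** Let h be the proportion of an arm admitted before halving. If those patients are left out,

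observed mean − full mean = −h × (mean of admitted − mean of not admitted).

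The bias in control minus active is the difference between two such terms. It vanishes if the terms are equal, or if admitted patients would have recovered at the same speed as the others.

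**Assumptions.** The protocol gives neither the admission rates nor the recovery times of admitted patients. I took gamma times with the section 5.1 mean of 6 and SD of 3 days (shape 4, scale 1.5), and no true effect on recovery time. The same admission mechanism acts in every arm, and no admitted patient has halved the score beforehand. Two mechanisms bracket the problem:

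- *Probabilistic:* the chance of admission rises with recovery time (logistic, slope 0.3 per day).
- *Threshold:* exactly the slowest are admitted, which is the extreme case.

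**Observed arm means at 10% v 5%** (full mean 6)

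| Mechanism | 10% admitted | 5% admitted | Shift in control − active |
|---|---|---|---|
| Probabilistic | 5.685 | 5.825 | −0.14 day |
| Threshold | 5.306 | 5.592 | −0.29 day |

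Formula check for the probabilistic row: −0.10 × (8.867 − 5.685) = −0.32 and −0.05 × (9.391 − 5.825) = −0.18; the difference is −0.14.

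**Type I error of the F test** (simulated, 130 per arm). At 10% v 5% it is about 6 to 7% under the probabilistic mechanism and about 13% under the threshold. With equal probabilistic admission in all arms it stays at 4.8 to 5.1%. The false signal favours the arm with more admissions.

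**Effect on a true 1-day benefit in all three active arms.** At 10% v 5% the estimate falls to about 0.84 to 0.86 day (probabilistic; 1 − 0.14 = 0.86) or about 0.73 day (threshold). Under the probabilistic mechanism, power falls from 83% with 5% admitted in every arm to 68%.

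**Other rates, probabilistic mechanism.** At 6% v 3% the shift is −0.10 day and type I error 5.1%. At 15% v 5% the shift is −0.26 day and type I error 9.9%.

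**The case against.** The strongest reply is that rules for missing values and intercurrent events usually sit in the SAP, which is not shown, and that nothing in the protocol says admitted patients are excluded. That is fair as far as it goes: no analysis set is defined, and a reader who infers that the protocol orders these patients dropped goes beyond the text. What remains is that the protocol itself fixes both halves of the problem: a diary that may end at admission, and a test that cannot represent a patient who has not reached the endpoint.

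Two further limits stand. The text lifts the duty to track but does not forbid it, so some patients may continue. A patient whose score halved before admission keeps a valid value. Both reduce the bias.

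Several stronger readings are tempting but unsupported:

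- *Sections 1.1 and 2.0 contradict each other.* The admission rule reads as a specific exception to the general 28-day rule, set beside the emergency-department rule.
- *Any difference in admission rates causes bias.* Admitted patients must also differ in recovery time.
- *Type I error approaches 28%.* That figure comes from deleting the top-ranked values in each simulated arm. Such trimming makes the F test reject about 10 to 15% of the time even when all arms are trimmed equally, so much of the excess is an artefact.
- *Up to 19% may be admitted, because section 1.2 reports 81% mild.* That figure describes confirmed cases in China. This trial enrols outpatients and excludes those hospitalised when tested.
- *Censoring at day 28 alone defeats ANOVA.* Under the planning assumptions, the chance of exceeding 28 days is about 1 in 100,000.

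**Conclusion.** The concern holds in a bounded form. The diary rule and the ANOVA together leave patients admitted or dead before halving without a primary outcome, and so select the analysed patients on an outcome that treatment may change. The comparison is biased when two conditions hold: admission differs by arm, and admitted patients would have recovered more slowly. If supplements prevent admission, the bias runs against them.

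At an assumed 10% v 5%, the shift is about 0.14 day under the probabilistic mechanism and at most about 0.29 day under the threshold, against a planned effect of 1 day. It would be about 0.10 day at 6% v 3% and is larger with wider gaps. These sizes rest on assumed admission rates, the gamma shape and a common admission mechanism. The structural gap does not depend on them. It should be closed before outcome data are seen, because a later change would look data-driven.

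**What to change.** Amend section 5.4 so that the primary analysis:

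1. Includes every randomised patient in a time-to-event comparison (log-rank or Cox) or a rank-based one.
2. Uses one stated time origin consistent with the endpoint: peak score as now defined, or randomisation if sections 2.1 and 5.2 are restated. It must say how the origin applies to a patient admitted before a peak has been observed. Starting the clock at day 0 without restating the endpoint would not match it.
3. Counts admission or death before halving as not reached through day 28, and censors other losses at the last diary entry.
4. Carries the multiplicity adjustment over to the new pairwise tests, in place of Tukey on means.
5. Keeps the ANOVA means as supportive.

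In section 1.1, state that the admission rule in section 2.0 is an exception to 28-day tracking.

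**Cost.** No new data are needed, because admissions and vital status are already collected (section 4.1). The effect is reported as a hazard ratio or median rather than a mean difference, and it now describes halving of symptoms without prior admission or death. The power statement in section 5.1 must be re-expressed for the new test.

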## **2.1 Primary Objective**

The primary objective will be evaluating the duration of symptoms in the four study arms. We will assess this by counting from when peak symptom score is achieved to when there is a 50% reduction in the symptom severity score.

## **3.0 Selection of Subjects**

### **3.1 Inclusion/Exclusion Criteria**

#### **Inclusion:**

A) 520 patients with a positive diagnosis of coronavirus 2019, managed in an outpatient setting, who are  $\geq 18$  years of age, divided into 4 groups as detailed above having any of the following symptoms

1. Fever or chills
2. Shortness of breath or difficulty breathing
3. Cough
4. Fatigue
5. Muscle or body Aches
6. Headache
7. New loss of taste

- 199 8. New loss of smell
- 200 9. Congestion or runny nose
- 201 10. Nausea
- 202 11. Vomiting
- 203 12. Diarrhea

204

205 B) Women of child bearing potential:

- 206 a. Have had a menstrual period within the past 30 days, or
- 207 b. Have had previous sterilization, or
- 208 c. Are perimenopausal (less than 1 year) who have a negative pregnancy test, or
- 209 d. Women of childbearing potential who do not meet the above and have a negative
- 210 pregnancy test.

211

212 **Exclusion:**

213 A) Patients who are hospitalized when they are tested for COVID-2019

214 B) Patients who reside outside of Ohio or Florida

215 C) Pregnant women

216 a. Current known pregnancy

217 b. Positive pregnancy test (women of child bearing potential who have not had

218 previous sterilization as defined as hysterectomy or tubal ligation. See above

219 inclusion criteria)

220 D) Women of childbearing potential who do not meet the above criteria, last

221 menstrual period greater than 30 days and have a positive pregnancy test.

222 E) Lactating women

223 F) End stage CKD (Chronic kidney disease)

224 G) Advanced liver disease awaiting transplant

225 H) History of Calcium Oxalate kidney stones.

226 **4.0 Study Procedures**

227 Prior to the initiation of participation, informed consent and permission to use protected  
 228 health information will be obtained via virtual or phone consent as per Cleveland Clinic  
 229 guidance, policies and procedures for COVID positive patients.

230 **4.1 Study Evaluations**

| Study Assessment                | Screening/Baseline
(Visits may occur in any of the following platforms:
Phone/Virtual/
Email)

(Window -1 or +2 days) | Daily through day 28
(Visits may occur in any of the following platforms:
Phone/Virtual/
Email)

(Window -1 or +2 days) | Day 7
(Visits may occur in any of the following platforms:
Phone/Virtual/
Email)

(Window -1 or +2 days) | Day 14
(Visits may occur in any of the following platforms:
Phone/Virtual/
Email)

(Window -1 or +2 days) | Day 21
(Visits may occur in any of the following platforms:
Phone/Virtual/
Email)

(Window -1 or +2 days) | Day 28
(Visits may occur in any of the following platforms:
Phone/Virtual/
Email)

(Window -1 or +2 days) |
|----------------------------------------|---------------------------------------------------------------------------------------------------------------------------------------------|-----------------------------------------------------------------------------------------------------------------------------------------------|--------------------------------------------------------------------------------------------------------------------------------|---------------------------------------------------------------------------------------------------------------------------------|---------------------------------------------------------------------------------------------------------------------------------|---------------------------------------------------------------------------------------------------------------------------------|
| Informed Consent                | X                                                                                                                                           |                                                                                                                                               |                                                                                                                                |                                                                                                                                 |                                                                                                                                 |                                                                                                                                 |
| Medical History                 | X                                                                                                                                           |                                                                                                                                               |                                                                                                                                |                                                                                                                                 |                                                                                                                                 |                                                                                                                                 |
| Symptoms                        | X                                                                                                                                           | X                                                                                                                                             | X                                                                                                                              | X                                                                                                                               | X                                                                                                                               | X                                                                                                                               |
| Medications Taking at Home      | X                                                                                                                                           | X                                                                                                                                             |                                                                                                                                |                                                                                                                                 |                                                                                                                                 |                                                                                                                                 |
| Study Supplementation Tablet(s) |                                                                                                                                             | X
(May start on Day 0 or Day1)                                                                                                             | X
(Through day 10)                                                                                                          |                                                                                                                                 |                                                                                                                                 |                                                                                                                                 |
| Emergency Room Visits           |                                                                                                                                             |                                                                                                                                               | X                                                                                                                              | X                                                                                                                               | X                                                                                                                               | X                                                                                                                               |
| Hospitalizations                |                                                                                                                                             |                                                                                                                                               | X                                                                                                                              | X                                                                                                                               | X                                                                                                                               | X                                                                                                                               |
| Change in Therapy               |                                                                                                                                             |                                                                                                                                               | X                                                                                                                              | X                                                                                                                               | X                                                                                                                               | X                                                                                                                               |
| Side Effects                    |                                                                                                                                             |                                                                                                                                               | X                                                                                                                              | X                                                                                                                               | X                                                                                                                               |                                                                                                                                 |
| Vital Status                    |                                                                                                                                             |                                                                                                                                               |                                                                                                                                |                                                                                                                                 |                                                                                                                                 | X                                                                                                                               |

|                                                                                     |                                                |  |  |  |  |  |
|-------------------------------------------------------------------------------------|------------------------------------------------|--|--|--|--|--|
| At home urine pregnancy test (women of child bearing potential as per I/E criteria) | X
*(Before taking first dose of study drug) |  |  |  |  |  |
|-------------------------------------------------------------------------------------|------------------------------------------------|--|--|--|--|--|

231

